#### Treatment notes

For this study, DHAP will be given in Eurartesim© tablets. While full product details are available from the manufacturers Sigma Tau (www.sigmatau.com), the following key issues are highlighted when administering DHAP, and summarised as a decision tree in Figure 5. DHAP is not recommended during the first trimester of pregnancy. Women of reproductive age (12-49) will be asked about their pregnancy status and if pregnant, the last time they felt the baby move. Any woman unsure of her pregnancy status will be offered a rapid pregnancy test, or referred to the nearest health facility. Women reporting that they are pregnant and have not felt the baby move (still in the first trimester), testing pregnant through the rapid pregnancy test or who are unsure of their pregnancy status will be tested with a malaria RDT and referred to the health center if testing positive. Pregnant women before the first trimester will not be treated with DHAP; pregnant women beyond the first trimester will be treated with DHAP. Additionally, DHAP should be administered with water no less than 3 hours after the last food intake, and no food should be taken within 3 hours after each dose. Any individual who does not wish to take, or cannot take DHAP, for whatever reason, will be offered the standard of care i.e. AL.

If a patient vomits within 30 minutes of taking DHAP, the whole dose will be re-administered. If a patient vomits within 30-60 minutes, half the dose will be re-administered. Re-dosing will not be attempted more than once. If the second dose is vomited, the patient will be referred to the nearest health centre. No more than two courses of DHAP will be given within a 12 month period, with a 2 month window between the two courses due to the long elimination half-life of piperaquine. Individuals identified during RFTAT responses who have been treated with DHAP in the previous 2 months, or twice within the previous year will be given AL.
[figure not shown]

Figure 5 - Decision tree for patient interactions during passive case detection at the health center/ health post and RFDA with DHAP in the community. mRDT, Malaria RDT; WRA, Women of Reproductive Age; HC, Health Center; DHAP, dihydroartemisinin-piperaquine. *due to previous dosing schedule.

## Study participants

Study participants will consist of three groups selected from residents of the health center catchment areas randomized to the control or intervention arms and will be selected as follows:

1. Individuals in households selected for endline sampling. Households will be identified as describe in section 2.5 (page 23)
2. Individuals living within 140 meters of an index case selected for a CHW-led reactive response (Figure 6)
3. Individuals living within 140 meters of an index case selected for a research team supported reactive response (see Section 2.4.1 and Figure 7), who will receive additional follow-up visits 3, 30 and 90 days after the initial reactive response.

## Reactive responses

All reactive responses will aim to take place within 7 days following presentation of an RDT positive incident malaria case to a health center or health post within the study areas. Based on work showing the spatial distribution of malaria infections in Southern Province ([name] dissertation, unpublished), all individuals residing within 140 meters of the index case household will be included in the reactive response. In the control (RFTAT) arm, the current standard of care will be provided in which individuals will be tested for malaria using an RDT. Positive individuals will be offered treatment with AL or referred to a health center according to national treatment guidelines. In the intervention (RFDA) arm, all individuals residing within 140 meters of the index case household will be offered DHAP. Testing with an RDT will not be performed in the RFDA arm, with the exception of research team responses (see Section 2.4.1 on page 20).

[figure not shown]

Figure 6 - Schematic of activities before and during a CHW reactive response. HC, Health Center; HP, Health Post; AL, artemether-lumefantrine. Seated / standing figures indicate individuals who are symptomatic or healthy respectively. The colour of individuals represents whether they are infected with P. falciparum (Red) or uninfected (black).

### Research Response

In order to assess parasite clearance and the risk of re-infection following a reactive response, a subset of index cases will be randomly selected for follow-up by a research team within each participating health center catchment area (Figure 7). Equal numbers of index cases will be randomly selected in each arm and in each clinic, with a minimum of two index cases per month in each arm i.e. minimum of four total per month. Only index cases reporting no history of travel will be enrolled. A questionnaire will be administered to all individuals participating in the reactive research responses and a finger prick blood sample will be obtained to collect dried blood spots (DBS) for study research purposes only. Participants will be adequately protected with risks minimized as much as possible during sample collection (see Section 3.1 for more information). Information collected through the questionnaire will include demographic information, current symptoms, recent malaria history, travel history, RDT result, HS RDT result (in RFDA arm only) and treatment administered (Appendix 6 and Appendix 7). Geocoordinates will be collected for each household targeted for a reactive response. Blood samples will be used to detect asexual stage parasites by PCR and all positive samples will be genotyped using a molecular bar code.

Follow-up visits will be conducted 3 (Appendix 9), 30 (Appendix 10) and 90 (Appendix 10) days after the initial reactive response. Additional information will be collected from each targeted individual on signs and symptoms of malaria, other treatments received, adherence to the drugs given (if any), and adverse reactions. A finger prick blood sample will be collected from each individual as a DBS at the 30 and 90 day follow-up visits. From the initial reactive response visit, blood samples will be used to detect asexual stage parasites by PCR and all positives genotyped using a molecular bar code.

For research responses enrolled in the RFDA arm, consenting individuals will be tested using the HS RDT as well as the standard RDT. No treatment decisions will be made based on the results from either the HS RDT or the standard RDT, rather they will all be offered DHAP. Individuals who do not consent to be enrolled in the RFDA arm will continue to receive the standard of care i.e. testing with a standard RDT and if positive, treatment given according to national policy.

[figure not shown]

Figure 7 – Schematic of activities before and during a reactive research response. HC, Health Center; HP, Health Post; AL, artemether-lumefantrine; DBS, Dried blood spot; DOT, Directly observed treatment. Seated / standing figures indicate individuals who are symptomatic or asymptomatic, respectively. The colour of individuals represents whether they are infected with *P. falciparum* (Red) or uninfected (Black).

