| **Primary data collection & sampling method** | Sampling after the interventions will be used to determine malaria seropositivity in children under fifteen in each health center catchment population.  The routine government rapid reporting system will be used to determine confirmed malaria case incidence throughout the entire study area.  Longitudinal cohorts will be used to determine clearance and re-infection rates for each arm from a subset of individuals participating in reactive responses. |
| **Sample size** | - Simple random sample survey of children under fifteen in all health clinic catchments population : 8,000 - Routine reporting for malaria case incidence: ~130,000 (all ages) - Reactive responses in all areas: ~30,000 (all ages) - Re-infection / importation / serology in a subset of the study participants: ~9,000 (all ages) |
| **Statistical & analytic plan** | A difference-in-differences approach will be used to assess changes in both primary and secondary outcomes among intervention and control groups, using mixed effects logistic and Poisson models for the outcomes of parasite seropositivity and confirmed malaria incidence. Clearance and prevention of reinfection from areas receiving rapid responses will be determined through Poisson regression. Month-by-month estimates of effectiveness will be analyzed using the routine rapid reporting of confirmed malaria incidence.  We will estimate direct effects and spillover effects of the reactive, focal malaria interventions on malaria incidence and prevalence and assess whether effects vary by intervention coverage, distance to intervention, and time from incident case detection. We will then pool this data with other similar trials using fixed and random effects. |

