All consenting individuals ≥ 1 month of age and < 15 years old in households participating in the surveys will be tested using an RDT and if positive given AL according to national treatment guidelines, or referred as appropriate e.g. if pregnant or suspected to be pregnant. Individuals will also be consented to provide finger prick blood samples (approximately 200 μL) collected as dried blood spots for:

- detection of asexual stage parasites by PCR
- serological responses to *P. falciparum* antigens
- serological responses to anopheline salivary peptides
- genotyping PCR positive samples using a molecular bar code

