**Outcomes**: Costs associated with RFTAT and RFDA, including personnel, transportation, and commodities.

**Inclusion/Exclusion criteria:** Not applicable. Study will use cost estimates and estimates of reduction in parasite prevalence as measured in Primary Aim.

**Procedures**: 1) randomization; 2) RFTAT with AL or RFDA with DHAP; 3) follow-up visit on day 3 to assess adverse reactions; 4) measurement of costs

**Analysis**: Detailed tracking of program expenditures on the establishment, production and delivery components of the RFDA and RFTAT interventions, including the value of time spent by the CHWs and other staff, will be used to calculate the financial costs. Costs will be calculated using an ingredients approach that involves enumerating both the quantity of specific inputs (e.g., hours spent, number of rapid diagnostic tests used, etc.) and the time spent during the intervention. As the analysis is intended to be incremental, existing infrastructure and recurrent inputs that would be present in the absence of the intervention will not be costed. The emphasis of the cost analysis is on determining the cost of RFDA and RFTAT alone, and not assessing the cost of training CHWs in the diagnosis and treatment of malaria nor in the follow-up visits to areas receiving reactive responses. Cost-effectiveness will then be measured through incident malaria cases averted as measured through the difference in malaria incidence at health centers in RFDA and RFTAT arms.

### Secondary Aim 4

Measure the proportion of *P. falciparum* infections likely attributable to importation and local transmission using parasite genotyping as well as defining genotypes spatial distribution.

Hypothesis: The proportion of *P. falciparum* infections attributable to importation will increase in both the intervention and control arms as local transmission is interrupted through the reactive case detection strategies. Additionally, the genetic diversity of locally transmitted parasites will decrease as transmission decreases but will be lower in communities receiving RFDA.

**Design**: nested cross-sectional study

**Population**: All individuals with a positive RDT for *P. falciparum* identified in the endline survey and during reactive case detection and their evaluation in reactive research responses.

**Outcomes**: Parasite population genetics, and spatial distribution of defined parasite genotypes.

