**Inclusion/Exclusion criteria:** All individuals tested for malaria during the endline survey as well as during reactive research responses who have consented to further analyses of their dried blood spot sample.

**Procedures**: Sample collection from 1) reactive responses; 2) endline survey; genotyping of PCR-positive samples

**Assays**: Genotyping of *P. falciparum* genomes using PCR-positive DBS

**Analysis**: All malaria infections will be geo-referenced through data collection. Spatial variation in the genomic complexity and diversity will be estimated using the Geneland

^34^package in R

^35^ which uses Bayesian methodology to identify clusters of individuals with similar genotypes while accounting for spatial dependence of geo-referenced data. The procedure is capable of analyzing multivariate gene outcomes including SNPs. The number of separate genetic populations in the study area will be estimated and mapped; migrants (*P. falciparum* infections dissimilar genetically from others in nearby space) will be classified as imported malaria cases without onward transmission and will also be identified and mapped. The influence of a number of environmental factors on the spatial distribution of malaria parasites will be estimated. The enhanced vegetation index available through remotely sensed data will provide an indicator of adult mosquito habitat

^36,37^. A digital elevation model will be used provide an indicator for the propensity of an area to harbor mosquito breeding sites

^38–40^. We aim to utilise spatio-genetic methods that have been utilized in various aspects of ecology, but have not yet been applied to malaria epidemiology to understand transmission dynamics in the two arms

^41^.

Genetic complexity, defined as the number of genetically unique parasites found within health centre and health post catchments, will be compared between RFDA and RFTAT areas using a Poisson or linear regression depending upon the number of genetically unique parasites found. A number of factors will be tested including proximity of the area to the main road, wealth of the area, vector control coverage of the area, age and demographics of the individuals living in the area, as well as environmental factors such as vegetation cover and topographical measures.

### Secondary Aim 5

Assess the utility of serology to measure short-term changes in malaria transmission and evaluate malaria elimination programs

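### Secondary Aim 4 compares parasite diversity by a raw genotype count that falls when fewer infections are genotyped, and its imported share from research responses is likely understated because travelling index cases are not enrolled

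*Protocol*

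**What the plan says.** **Diversity.** Secondary Aim 4 (section 2.8.5) predicts that the diversity of locally transmitted parasites will be lower in RFDA communities. Genetic complexity is the between-arm measure: "the number of genetically unique parasites found within health centre and health post catchments, will be compared between RFDA and RFTAT areas". The comparison is by Poisson or linear regression, the choice depending on how many unique parasites turn up. The factors named for testing are road proximity, wealth, vector control, demographics and environment. The number of infections genotyped is not among them. Secondary Aim 2, by contrast, does specify an offset, the number of people who gave a dried blood spot.

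**Importation.** Research responses (section 2.4.1) are set up "In order to assess parasite clearance and the risk of re-infection following a reactive response", and the rule is "Only index cases reporting no history of travel will be enrolled". No look-back period for travel is given. The Project summary uses the same subset for importation: "Re-infection / importation / serology in a subset of the study participants: ~9,000 (all ages". The Aim 4 inclusion criterion is "All individuals tested for malaria during the endline survey as well as during reactive research responses", provided they consented to further analysis of the blood spot. The endline survey (section 2.5) tests "All consenting individuals ≥ 1 month of age and < 15 years old in households participating in the surveys"; it records travel history and does not exclude on it. Imported status is assigned genetically: "infections dissimilar genetically from others in nearby space) will be classified as imported malaria cases without onward transmission". The hypothesis is that the proportion of "infections attributable to importation will increase in both the intervention and control arms as local transmission is interrupted". Whether the two sources are pooled is not stated.

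**The concern.** A count of distinct genotypes depends on two things: how varied the parasite population is, and how many infections were examined. The Aim 4 hypothesis is about the first, but the outcome mixes both. RFDA is expected to lower the number of infections, so the comparison can appear to confirm lower diversity when only the number of infections differs.

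The travel rule suits Aim 2, which asks about clearance and re-infection. For Aim 4 it removes the index cases most likely to be imported, together with their neighbourhoods. Responses by community health workers alone cannot fill the gap, because Table 2 (section 2.7) shows blood-spot consent only for the endline survey and the research responses. The protocol does not mention this restriction under Aim 4.

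Section 1.4 presents genotyping as potential evidence for directing elimination work and documenting zero transmission. A count that favours RFDA and an understated imported share would both weaken that use.

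**Working it through.** The protocol gives no sample size, expected genotype count or expected imported share for Aim 4, so there is no stated figure to reproduce. All values below are assumptions unless a source is named.

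**1. Raw count, same parasite population in both arms.** With G equally common genotypes and N infections genotyped, the expected number of unique genotypes is G × (1 − (1 − 1/G)^N).

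| G | N = 40 | N = 20 | Ratio of counts | Ratio per infection genotyped |
|---|---|---|---|---|
| 20 | 17.43 | 12.83 | 0.74 | 1.47 |
| 50 | 27.71 | 16.62 | 0.60 | 1.20 |
| 200 | 36.34 | 19.08 | 0.53 | 1.05 |

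The true diversity ratio is 1 in every row. The last column is the count ratio before rounding × 40/20, which is what an offset of log(number genotyped) would estimate. It errs in the other direction because the count saturates as N grows.

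**2. The protocol's planning figures as stand-ins.** Section 2.9 gives about 500 children per catchment and seropositivity of 5% against 1.78%. Treating these rates as infection prevalence (an assumption) gives 500 × 0.05 = 25 and 500 × 0.0178 = 8.9, about 9, infections per catchment. The same formula then gives count ratios of 0.87 (5 equally common genotypes), 0.56 (15), 0.42 (50) and 0.37 (500). The corresponding offset ratios are 2.41, 1.56, 1.16 and 1.02.

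**3. Simulation.** There were 8 catchments per arm, means of 25 and 8.9 infections, a between-cluster coefficient of variation of 0.5 (section 2.9), an identical genotype pool in both arms, and 1,000 runs for each of four pools. Poisson regression used a scale correction and a t reference on 14 degrees of freedom.
- Raw count: mean ratios from 0.80 to 0.43. A difference was declared in 44% to 90% of runs at a nominal 5%.
- Richness rarefied to 4 infections: mean ratio 0.999 to 1.002. A simple t-test rejected in 6% to 10% of runs.
- Simpson diversity (expected heterozygosity): mean difference −0.002 to +0.002. A simple t-test rejected in 7% to 12% of runs.

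The standardised measures remove the bias. The small remaining excess in rejections concerns the choice of test with few clusters and uneven precision.

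**4. Importation, sensitivity only.** Let f be the true imported share, s the fraction of imported index cases removed by the travel question, and w the fraction of genotyped infections that come from research responses. Suppose every infection in a focus shares its index case's origin, and the endline survey returns f. Then

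observed share = w × f(1 − s) / [f(1 − s) + 1 − f] + (1 − w) × f.

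For f = 30%:
- s = 0.5, w = 0.3: 0.15/0.85 = 0.176; 0.3 × 0.176 + 0.7 × 0.30 = 26%
- s = 0.9, w = 0.53: 0.03/0.73 = 0.041; 0.53 × 0.041 + 0.47 × 0.30 = 16%
- s = 1, w = 0.8: 0.2 × 0.30 = 6%
- s = 1, w = 1: 0%

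The value w = 0.53 is 9,000/(9,000 + 8,000) from the Project summary; it is a share of people, not of infections. The shared-origin assumption is extreme, so these figures bound the bias and do not estimate it.

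**5. Time.** Research responses run during the intervention, while the endline survey takes place only at two years (section 2.1). With f constant at 30% and s = 0.5, the same model gives 17.6% from research responses and 30% from the survey. Pooling or comparing the sources over time would then show a rise, as hypothesised, with no change in importation.

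**The case against.** **On diversity.** Research responses are equal in number by arm and clinic, and about 500 children are surveyed per catchment, so the count is a fair measure of distinct genotypes found per catchment. Aim 4 also includes a spatial Bayesian analysis of complexity and diversity. The artefact needs RFDA to lower infections, and it is mild if few genotypes circulate (0.87 with five). An adjustment could be added in a statistical analysis plan, which is not at hand. These points limit the size of the problem, but the protocol itself fixes the between-arm outcome as a raw count while its hypothesis concerns diversity.

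**On importation.** The rule excludes travelling index cases, not travellers. Everyone within 140 m of an enrolled index case is eligible from 1 month of age, and their own travel is recorded. Imported status is assigned from genetics, and the endline survey has no travel filter. All of this stands.

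Four stronger readings are tempting, and the documents do not support them:
- That imported infections are screened out altogether. Travelling neighbours, and children at endline, can still contribute them.
- That all Aim 4 samples come from travel-filtered foci. The endline survey is a second source.
- That the understatement can be given a figure. The inputs f, s and w are not in the protocol.
- That the comparison of importation between arms is biased. The rule is the same in both arms, so it affects the level of the share more clearly than the contrast.

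**Conclusion.** The diversity point holds. Followed as written, the raw-count comparison can support the hypothesis of lower diversity under RFDA when diversity is equal. The expected count ratio is 0.74 to 0.53 for half as many infections and 20 to 200 equally common genotypes. It is closer to 1 if very few genotypes circulate, and there is no artefact if the arms yield equal numbers of infections.

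The importation point holds in a limited form. The share estimated from research responses, and any figure pooled with the endline survey, is likely too low by an unknown amount. The direction rests on two assumptions: that reported travel marks imported index cases, and that infections near an index case tend to share its origin. The under-15 survey limits the bias in a pooled figure but does not remove it, and it says nothing about adults.

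Aim 4 is secondary, and neither point touches the primary outcome.

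**What to change.** **Diversity.** In Secondary Aim 4, replace the raw count as the between-arm measure with rarefied richness or expected heterozygosity. An offset of log(number genotyped) should not be used instead, since it over-corrects (section 2.8.5 outcome: 1.05 to 1.47 in the first table). The raw count may stay as a descriptive figure beside the number genotyped. If rarefaction is chosen, state the depth, and state how catchments with fewer infections than that depth are handled.

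**Importation.** Report the imported share separately for research responses and for the endline survey. Do not pool the two or compare them across time. Label the first as applying to infections around non-travelling index cases and the second as applying to children under 15. Log the travel status of every index case screened, so that the number excluded is known. This log cannot support reweighting, because no foci of travelling index cases are enrolled and there is nothing to weight up. Drawing some research responses irrespective of travel would widen the claim, but it takes responses from Aim 2, where the guaranteed minimum is two index cases per arm per month. It is a trade-off and not part of this recommendation.

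**Cost.** Protocol wording, one logged field, slightly more analysis work and a narrower importation claim. No extra samples are needed.
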